### **Tumor Response**

Response and progression will be evaluated in this study using the international criteria proposed by the Response Evaluation Criteria in Solid Tumors (RECIST) Committee [JNCI 92(3):205-216, 2000]. Changes in only the largest diameter (one-dimensional measurement) of the tumor lesions are used in the RECIST v1.1.

### **Best Overall Response**

Best response is the maximal response recorded from the start of a treatment until the end of treatment taking into account any requirement for confirmation.

### **Progression-Free Survival**

Progression-free survival (PFS) is defined as the duration of time from the start of a treatment until objective tumor progression or death.

### **Overall Survival**

Overall survival (OS) is defined as the duration of time from the start of treatment to death.

### **Change in Resectability**

For those patients in Group 1 who are classified as having unresectable disease (as opposed to being medically unfit), their disease will be assessed throughout the study to determine if

treatment leads to their disease becoming resectable as deemed by two surgeons. Resectability is based upon tumor location, vascular involvement, and technical feasibility issues.

## **Adverse Events**

Adverse events will be evaluated by the NCI Common Terminology Criteria for Adverse Events CTCAE version 4.03 (<http://ctep.cancer.gov/reporting/ctc.html>) to determine the incidence of serious adverse events, as defined below.

### **5.4.1 Adverse Event Monitoring**

Information about all adverse events, whether volunteered by the subject, discovered by investigator questioning, or detected through physical examination, laboratory test or other means, will be collected and followed as appropriate by the patient's treating physician.

This study will document all serious adverse events (as defined below in section 5.4.2 – Definitions) experienced by a subject while they are participating on the study and for 4 weeks after discontinuation of the matched and/or unmatched regimens chosen by their treating physician based on study navigation, or the start of a new therapy (whichever comes first).

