| Duration of administration            | 
Arm A
 
 
• Groups 1 and 2 = <math>\sim 8</math> week cycles of a regimen of <math>\geq 1</math> drug that targets molecular alteration(s) followed by disease appropriate imaging (i.e., PET-CT vs. CT vs. MR imaging) followed by crossover to treating physician's choice of systemic chemotherapy for SD or PD per RECIST, or unacceptable toxicity but to remain on I-PREDICT recommended regimen if CR, PR by RECIST 1.1
 
• Group 3 = <math>\sim 8</math> week cycles of a regimen of <math>\geq 1</math> drug that targets molecular alteration(s) followed by disease appropriate imaging (i.e., PET-CT vs. CT vs. MR imaging) with cessation of therapy if PD or unacceptable toxicity
 
 
Arm B
                                                                                                                                                                                                                                                                                                                                                                                                                                                                                                                                |

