#### **Exploratory Endpoints**

Estimate the:

1. Overall response rate (ORR) defined as partial (PR) or complete response (CR) occurring at any point during treatment according to Response Criteria in Solid Tumors (RECIST) 1.1 in all treatment groups
2. Regression rate as a percent defined by best percent size reduction in target lesions from baseline to discontinuation in all groups
3. Progression free survival (PFS) defined as time from first dose to disease progression or death, whichever occurs first
4. Overall survival (OS) defined as time from first dose to death due to any cause
5. Resection rate as a percent of patients previously considered unresectable that are able to be resected in all groups
6. Change in biochemical tumor markers of disease as defined as the best percent change from baseline in relevant tumor markers from first dose to discontinuation
7. Incidence of serious adverse events in all groups according to CTCAE v4.03

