### **Study Group 1 and Group 2 (treatment naïve)**

ARM A:

A matched treatment regimen will be administered for approximately 8 weeks as dictated by recommendations for approved anti-cancer agents or as dictated by clinical trials. Disease-appropriate imaging (i.e., PET-CT vs. CT vs. MR imaging) will be performed at approximately week 8 according to standard of care or required clinical trial practices. Objective tumor response will be determined according to RECIST v1.1 and this First Response assessment will guide subsequent treatment according to the following:

3. Patients demonstrating a PR or CR per RECIST 1.1 will continue treatment until
  - a complete response persists for at least six months
  - the tumor becomes resectable
  - their tumor response declines to SD or PD
  - they experience unacceptable toxicity.

4. Patients demonstrating SD or PD per RECIST 1.1 will be removed from matched therapy and placed onto the treating physician's choice of systemic chemotherapy appropriate to their disease. Alternatively, the treating physician may continue matched therapy at their discretion if there are no effective traditional systemic chemotherapy regimens available.

Patients who experience SD but short of PR while on matched treatment may, after experiencing progressive disease while receiving treating physician's choice of systemic chemotherapy appropriate to their disease, return to their prior matched treatment and will be monitored again for benefit. The degree of objective tumor response observed at the patient's First Response Assessment on the original matched treatment, will then guide subsequent treatment according to the following:

1. Patients demonstrating a 10-29% decrease in the sum of diameters of target lesions (First Response Assessment) will resume treatment with the original matched treatment regimen. Treatment will continue until:
  - a complete response persists for at least 6 months,
  - their tumor becomes resectable,
  - they experience progressive disease (PD), or
  - they experience unacceptable toxicity.
2. Patients demonstrating a <10% decrease in the sum of diameters of target lesions (First Response Assessment) will then receive the traditional second-line standard of care treatment appropriate for their disease.

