### **6.6 Exploratory Analyses**

Exploratory analyses will be conducted to evaluate efficacy and adverse event outcomes in each group and ARM and for comparison across groups.

All exploratory analysis will test the hypothesis of greater response rate in Arm A than that in Arm B. With an estimated sample size of 30 (ARM A) and 45 (ARM B) in each group, we can estimate the response rate with a standard error no larger than 0.09 and 0.07, respectively. We will have sufficient statistical power to detect the difference between groups only if the difference between groups is sufficiently large. For example, with the sample size of 30 and 45 for Arm A and Arm B, we will have 79% power to detect the response rate of 0.25 and 0.05 between the two arms with one-sided 10% type I error rate using the continuity corrected chi-square test.

We will have more than 80% power to detect the difference between Arm A and Arm B using the log-rank test when the median PFS is 4 months and 2 months for the two arms, respectively.

In addition, in Group 1A, we will estimate the proportion of patients who are initially unresectable but converted to resectable after 8 weeks of the matched treatment, or if ever resected. With 30 patients, we expect to see at least one patient becomes resectable with a probability of 0.79, 0.96, and 0.99 if the conversion rate is 0.05, 0.10, and 0.15, respectively. We expect to see at least 2 patients become resectable with a probability of 0.82 and 0.95 if the conversion rate is 0.10 and 0.15, respectively. One-sided nominal level at 10% will be used to declare statistical significance. No P value adjustment for multiplicity will be applied due to the exploratory nature of the study. All study results need to be confirmed by future studies with larger sample sizes.

- The response rate (proportion of patients reaches CR or PR) will be estimated based on RECIST for each patient group and each treatment arm.
- The tumor regression rate (in %) will be calculated by the percent tumor size reduction from baseline to after treatment will be determined in and across patient groups.
- Progression-free survival (PFS) and overall survival (OS) will be determined in and across patient groups and treatment arms.

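### In Groups 1 and 2 the SAE window is undefined at crossover, so crude SAE incidence by arm is distorted by unequal follow-up or by crossover attribution

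*Protocol*

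**What the plan says.** - **Collection window.** Protocol 5.4.1 documents SAEs during study participation and "for 4 weeks after discontinuation of the matched and/or unmatched regimens chosen by their treating physician based on study navigation". The same sentence then adds an earlier cut-off: "or the start of a new therapy (whichever comes first". It does not define a new therapy and does not mention crossover.
- **Arm A, Groups 1 and 2.** Under Study Group 1 and Group 2 (treatment naïve), the rule at the first assessment (about week 8) is "Patients demonstrating SD or PD per RECIST 1.1 will be removed from matched therapy"; they then go to chemotherapy chosen by the physician. The Study Summary describes matched treatment as "followed by crossover to treating physician's choice of systemic chemotherapy for SD or PD per RECIST, or unacceptable toxicity". There is one exception: "Alternatively, the treating physician may continue matched therapy at their discretion if there are no effective traditional systemic chemotherapy regimens available". Some patients with stable disease may later return to the matched regimen.
- **Arm B.** The Study Summary (Duration of administration) lists four stops: progression, unacceptable toxicity, a complete response lasting 6 months, and becoming resectable. Stable disease is not among them.
- **Measure.** The exploratory endpoint is "Incidence of serious adverse events in all groups according to CTCAE v4.03". Exploratory objective 2 asks for that incidence under matched treatment and under chemotherapy. Section 6.6 will "evaluate efficacy and adverse event outcomes in each group and ARM and for comparison across groups". The adverse event analysis plan gives frequency tables of Grade 3-5 toxicities by incidence, patient, disease, drug and drug combination. No time at risk appears in any of these places.

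**The concern.** A crude incidence rises with the time a patient is watched. Here that time depends on the arm by rule: the same finding, stable disease at week 8, ends the assigned regimen in Arm A but not in Arm B. Whether this shortens or lengthens Arm A's SAE window turns on the undefined clause in 5.4.1.

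At stake is exploratory objective 2. Two drugs with the same toxicity per month could show different SAE percentages, and the sign of the difference would depend on how sites read one clause. Events left undocumented after crossover cannot be recovered at the analysis stage.

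**Working it through.** **No stated figure to reproduce.** The protocol gives no SAE rate, observation time or SAE power. What follows is an illustration under declared assumptions.

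**Inputs from the protocol**
- Scan interval of about 8 weeks: d = 56/30.44 = 1.84 months.
- Illustrative Arm A response rate 0.25 and Arm B median PFS 2 months (section 6.4, reading the figures there in the order Arm A, Arm B).
- Expected 30 patients in Arm A and 45 in Arm B per group.

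**Assumptions**
- Equal, constant hazard h of a first SAE in both arms: 0.05 to 0.10 per month.
- Exponential PFS, with progression found at the next 8-weekly scan.
- Arm A responders stay on matched therapy for a further median of 4 to 6 months.
- Arm B median PFS of 4 months as an alternative to 2.
- No 4-week tail, no return to matched therapy, no use of the exception that keeps patients on matched therapy.

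**Formulas**
- Probability of progression by a given scan, for median m: p = 1 − exp(−d·ln2/m). This is 0.471 for m = 2, 0.273 for m = 4 and 0.191 for m = 6.
- Mean time to the stopping scan: d/p = 3.9, 6.7 and 9.6 months.
- Chance of no SAE up to that scan: G(m) = p·e/(1 − (1 − p)·e), with e = exp(−h·d). At h = 0.05, e = 0.912, G(2) = 0.830, G(4) = 0.739.
- Arm B crude incidence: 1 − G(m_B).

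**Reading 1: crossover chemotherapy is a new therapy and closes the window.** Arm A incidence is 1 − e·(0.75 + 0.25·G(m_resp)).
- At h = 0.05, m_resp = 4: 1 − 0.912 × (0.75 + 0.25 × 0.739) = 14.7%.
- Arm B, 2-month median: 1 − 0.830 = 17.0%, ratio 0.87. Arm B, 4-month median: 26.1%, ratio 0.57.
- Mean observation in Arm A is 1.84 + 0.25 × 6.7 = 3.5 months (4.2 if responders last a further median of 6 months), against 3.9 or 6.7 months in Arm B.

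| Arm B median PFS | Ratio A/B over h = 0.05–0.10, m_resp = 4–6 |
|---|---|
| 2 months (plan's illustration) | 0.86–0.97 |
| 4 months (assumed) | 0.57–0.65 |

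The true ratio is 1.0 throughout. The gap is small at 2 months because 47% of Arm B also stops at the first scan for progression. The asymmetry comes from patients with stable disease, not from all non-responders.

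**Reading 2: crossover chemotherapy is a navigated regimen, the window runs through it, and events stay with Arm A.** PFS on crossover chemotherapy is assumed equal to Arm B PFS. Arm A incidence is 1 − e·(0.25·G(m_resp) + 0.75·G(m_B)).
- At h = 0.05, m_resp = 4, m_B = 2: 1 − 0.912 × (0.25 × 0.739 + 0.75 × 0.830) = 26.3%, against 17.0%, ratio 1.55.
- Over the same ranges the ratio is 1.48–1.65 with a 2-month Arm B median and 1.23–1.31 with 4 months.

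**Noise.** For Reading 1 at h = 0.05 and a 2-month median, the gap is 17.0 − 14.7 = 2.3 points. Its standard error with 30 and 45 patients is √(0.147 × 0.853/30 + 0.170 × 0.830/45) = 8.6 points.

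**Check of the remedy.** In this model, events per patient-month equal h in both arms, and the incidence in the first 8 weeks is 1 − e in both arms: 8.8% at h = 0.05 and 16.8% at h = 0.10.

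**The case against.** A reader might infer that matched therapy will look safer by design, because the window shuts at week 8 for every Arm A non-responder who crosses over while Arm B is watched to progression. The protocol does not support that.
- Closure at crossover is only one reading. Crossover chemotherapy is protocol-directed and chosen by the treating physician, so it can count among the matched or unmatched regimens that 5.4.1 follows. The direction is then reversed.
- Progression ends treatment in both arms, Arm B has other stops, and some Arm A patients may stay on or return to matched therapy.
- At the plan's own illustrative 2-month median, the Reading 1 bias is well below sampling noise in one group.

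Other points on this side also carry weight. Adverse events are to be described, no Arm A versus Arm B SAE test is specified, and the comparison named in 6.6 is across groups. Tabulation by drug and combination already helps attribution. The tables so specified are of Grade 3-5 toxicities, and no denominator is named, so incidence per patient is an inference. Exposure-adjusted rates are commonly left to a statistical analysis plan, which is not shown, so their absence alone is no fault.

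What this does not answer is the window itself. Section 5.4.1 decides which SAEs are documented at all, a later analysis plan cannot restore events that were never collected, and drug tables without time at risk still mix toxicity with length of follow-up.

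**Conclusion.** The point holds in a limited form. The rules give unequal treatment time for patients with stable disease in Groups 1 and 2, and 5.4.1 leaves open whether their SAE window closes at crossover. Under either reading, the by-arm incidence does not isolate matched treatment: it is distorted by shorter follow-up in one case and by chemotherapy events counted in Arm A in the other.

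Under the closing reading the distortion is slight at the plan's 2-month Arm B median and material only if Arm B PFS is longer, which the protocol does not state. These sizes rest on assumed equal, constant hazards and exponential PFS; only the existence of the asymmetry and the undefined clause come from the text. The endpoint is exploratory, so this is a minor issue.

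**What to change.** 1. In 5.4.1, state whether crossover chemotherapy closes the SAE window. Preferably keep documenting SAEs for the full 4 weeks after matched therapy stops, even if chemotherapy has begun.
2. Tabulate SAEs and Grade 3-5 events by the regimen being received at onset. Flag events that occur on crossover chemotherapy within 4 weeks of stopping matched therapy, so that delayed toxicity is not silently charged to chemotherapy.
3. Beside overall crude incidence, report events per patient-month of observation and crude incidence in the first 8 weeks, a window common to both arms apart from early stops.

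The cost is a little extra tabulation. Applying 5.4.1 already requires start, stop and new-therapy dates; the preferred window adds up to 4 weeks of SAE documentation after crossover. Rates per patient-month assume a roughly constant hazard, which the 8-week table helps to check. No treatment rule changes.

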### **5.4.2. Definitions**

#### **Adverse Event**

An adverse event (AE) is any undesirable sign, symptom or medical condition occurring after starting treatment even if the event is not considered to be related to the treatment.

Medical conditions/diseases present before starting treatment are only considered adverse events if they worsen after starting treatment.

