#### **Relationship**

Attribution categories for adverse events in relationship to treatment are as follows:

Definite – The AE *is clearly related* to the study treatment.

Probable – The AE *is likely related* to the study treatment.

Possible – The AE *may be related* to the study treatment.

Unlikely – The AE *is doubtfully related* to the study treatment.  
Unrelated – The AE *is clearly NOT related* to the study treatment.

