### **Seriousness**

A serious adverse event is an undesirable sign, symptom or medical condition which:

- 
- is fatal or life-threatening
  - required or prolonged hospitalization
  - results in persistent or significant disability/incapacity
  - constitutes a congenital anomaly or a birth defect
  - is medically significant, may jeopardize the subject and may require medical or surgical intervention to prevent one of the outcomes listed above.
- 

Events not considered to be serious adverse events are hospitalizations for the:

- routine treatment or monitoring of the studied indication not associated with any deterioration in condition.
  - elective or pre-planned treatment for a pre-existing condition that did not worsen.
  - treatment on an emergency, outpatient basis for an event not fulfilling any of the definitions of serious given above and not resulting in hospital admission.
- 

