### **Analysis Plan for adverse events**

Treatment adverse events will be evaluated by the NCI Common Terminology Criteria for Adverse Events CTCAE version 4.03 (<http://ctep.cancer.gov/reporting/ctc.html>). Analyses will be performed for all patients enrolling to the study that subsequently receive matched therapy or physician's choice of traditional systemic chemotherapy. Frequency tabulation for all toxicities Grades 3-5 will be generated by the following:

- **Incidence.**
- **Patient.**
- **Disease.**
- **Drug.**
- **Drug combination (Note: given the infinite number of potential drugs and combinations, we cannot ascertain this *a priori*).**

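### SAE incidence as defined includes serious progression of, and death from, the cancer under study, so it cannot be read as a measure of drug safety; the Grade 3-5 tables do not say which events they count

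*Protocol*

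**What the plan says.** Protocol 5.4.2 (Adverse Event) covers any untoward condition "occurring after starting treatment even if the event is not considered to be related to the treatment". For disease already present at the start it adds: "Medical conditions/diseases present before starting treatment are only considered adverse events if they worsen after starting treatment".

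Under Seriousness, an event qualifies if, among other things, it "is fatal or life-threatening" or involves hospital admission. One exclusion mentions the disease being studied: admission for "routine treatment or monitoring of the studied indication not associated with any deterioration in condition".

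Section 5.4.1 collects SAEs during participation and "for 4 weeks after discontinuation of the matched and/or unmatched regimens chosen by their treating physician based on study navigation", or until a new therapy starts if that is sooner.

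Exploratory objective 2 asks for SAE incidence on matched therapy and on chemotherapy. Item 7 of the Exploratory Endpoints is: "Incidence of serious adverse events in all groups according to CTCAE v4.03". Section 6.6 plans adverse-event analyses by group and arm and comparisons across groups.

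A five-level scale from definite to unrelated is introduced under Relationship: "Attribution categories for adverse events in relationship to treatment are as follows". In the Analysis Plan for adverse events, the tabulation rule is: "Frequency tabulation for all toxicities Grades 3-5 will be generated by the following". The breakdowns listed are incidence, patient, disease, drug and drug combination. Attribution is not among them.

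**The concern.** Every participant enters with a cancer expected to worsen, and for many to be fatal within two years. A definition that counts worsening of pre-existing disease regardless of cause, with no separate provision for the study cancer, brings part of the disease course into the safety endpoint.

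This matters because the SAE figure is to be reported for matched therapy and for chemotherapy. Patients are placed in arms by the treatment they received, not by randomization (section 6.1), and the study is histology-agnostic. An arm or group with more lethal or faster-progressing tumors can show more SAEs on equally safe drugs, and slower progression can look like better safety. The definition also decides what sites must report to the Principal Investigator within 24 hours (5.4.4), so a later analysis plan cannot wholly repair it.

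**Working it through.** The plan states no figure on this point, so the main check is of the text.

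**Step 1: is worsening of the study cancer an adverse event?** Relatedness is not required, and a disease present beforehand counts once it worsens. The study cancer is such a disease, and no section excludes it. Taken literally, yes.

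**Step 2: is it serious?** Yes, if it is fatal or life-threatening, leads to admission or meets another listed criterion. The exclusion naming the studied indication covers only admissions without deterioration. The neighbouring one, for pre-existing conditions, also requires that the condition did not worsen. Neither removes an admission for a deteriorating cancer. Progression that meets no seriousness criterion is not an SAE.

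**Step 3: is it inside the window?** Only up to 4 weeks after the regimen stops, or the start of a new therapy if sooner. Later cancer deaths fall outside, unless survival follow-up is taken to be part of study participation, which 5.4.1 leaves open.

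**Step 4: does the analysis separate it?** Exploratory objective 2 and endpoint item 7 have no relatedness filter. By contrast, Safety Stopping Rules a and b are limited to drug-related events, so the protocol states that restriction where it intends it.

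**Step 5: the Grade 3-5 tables.** Sections 6.4 and 6.6 refer to treatment adverse events and the tabulation to toxicities; neither term is defined as related or all-cause. Stopping rule b adds a drug-related qualifier to toxicities, which suggests the bare word may be wider. Against that, the stopping-of-treatment lists keep progression and unacceptable toxicity apart. Both readings are open.

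**Size, deaths (illustration only).** Inputs: the 2-year mortality m in Figure 1, a constant hazard, and 12 weeks (one course of about 8 weeks plus the 4-week window), with 2 years taken as 104 weeks. The formula is P = 1 − (1 − m)^(12/104).

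| Tumor type | m | P(death by week 12) |
|---|---|---|
| Entry threshold | 50% | 7.7% |
| Breast, Stage IV | 52.1% | 8.1% |
| Colorectal, Stage IV | 58.6% | 9.7% |
| Lung (non-small cell), Stage IV | 88.7% | 22.2% |
| Pancreas, Stage IV | 93.3% | 26.8% |
| Gallbladder, Stage IV | 94.8% | 28.9% |

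**Size, progression (illustration only).** Inputs: the planning median PFS of 4 months (Arm A) and 2 months (Arm B), and arm sizes of 30 and 45 (section 6.6), with exponential times. Eight weeks is 8 × 7 / 30.4375 = 1.84 months.

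- Arm A: 1 − 2^(−1.84/4) = 27%, about 8 of 30.
- Arm B: 1 − 2^(−1.84/2) = 47%, about 21 of 45.

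These are ceilings on what progression by week 8 could add, since only progression meeting a seriousness criterion counts.

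**The case against.** The strongest reply is that counting events whatever their cause is a coherent choice. An all-cause incidence makes no claim of harm, the attribution scale lets a cancer death be recorded as unrelated, and removing progression brings in a subjective judgement in an open-label study. Table layouts are commonly left to an analysis plan, which is not shown here. The endpoint is exploratory, the last of seven, in a study that calls itself hypothesis-generating.

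Much of this stands. A reader might infer that the protocol presents cancer deaths as treatment harm; it does not. A reader might also infer that such deaths are credited to individual drugs in the Grade 3-5 tables; the undefined terms do not establish that, and a breakdown by disease is planned there.

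The size must be read with the same care. The calculation makes no allowance for selection on ECOG 0-1 and adequate organ function, treats Figure 1 mortality as cancer death, and ignores closure of the window when a new therapy starts. Under section 3.2, Group 1 and 2 Arm A patients with stable or progressive disease at about week 8 are generally moved to chemotherapy, which would close it. The gap between pancreas and colorectal (26.8% − 9.7% = 17.1 points) might be taken as a plausible arm difference. It would need one arm made up wholly of each tumor, which the 65% cap on gastrointestinal cancers rules out across the trial.

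The objection does not dispose of the definition itself. It belongs to the protocol, and the SAE endpoint built on it does not use the attribution collected.

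**Conclusion.** The point holds in a limited form. As 5.4.2 is written, serious deterioration of the study cancer and death from it within the window count as SAEs, and SAE incidence is reported with no relatedness filter. It therefore partly repeats the PFS and OS events and cannot by itself support a statement about the safety of matched therapy against chemotherapy. For the Grade 3-5 tables the finding is ambiguity only.

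The range of roughly 8% to 29% deaths in 12 weeks rests on a constant hazard and Figure 1 mortality. It is an upper range across tumor types, not a forecast of a difference between arms.

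The primary feasibility endpoint is not touched, nor are stopping rules a and b provided attribution is applied. The change is worth making because it is cheap and the safety description is otherwise hard to interpret.

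**What to change.** 1. In 5.4.2, state how progression of the study cancer, and hospitalization or death due to it, is recorded, and list those events separately from other SAEs.
2. For endpoint item 7 and in section 6.6, report SAE incidence and Grade 3-5 events both all-cause and treatment-related (definite, probable or possible on the existing scale), with deaths split into progression and other. This also settles what the Grade 3-5 terms mean.
3. State which table supports safety statements about matched therapy and chemotherapy.

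The cost is a short addition to 5.4.2 and an extra table column built from attribution categories the protocol already defines. The downside is that judging an event due to progression or to treatment is subjective when treatment is open-label, so the all-cause table should stay beside the treatment-related one.
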